### Study endpoint

2.7

Main study endpoints include neurocognitive functioning, which can be assessed by:
Subjective cognitive measures: The Cognitive Complaints in Bipolar Disorder Rating Assessment (COBRA) (Rosa et al., 2013).Objective cognitive measures: The Stroop Color and Word Test (SCWT) (Golden, 1978), the categorical verbal fluency test (CVFT) (animal naming) (Chen et al., 2000), Chinese Auditory Verbal Learning Test (C‐AVLT) (Lee et al., 2002), and the Trail Making Test Part B (TMT‐B) (Lu & Bigler, 2000); the Digital Span Forward and Backward subtest (DSFB) and the Digit Symbol Coding subtest (DSC) of the Wechsler Adult Intelligence Scale‐Revised by China (WAIS‐RC) (Gong, 1982) and Trail Making Test Part A (TMT‐A) (Lezak et al., 2004); and the Visual Reproduction subtest (VRP) and the Visual Recognition subtest (VRC) of the Wechsler Memory Scale‐Revised (WMS‐R) (Gong, 1987).

Secondary study endpoints are as follows: Global Assessment Function (GAF), Methods Checklist on Quality of Life issued by World Health Organization‐Brief version (WHOQOL‐BRIEF), Pittsburgh Sleep Quality Index (PSQI), Positive and Negative Affect Scale (PANAS), and neuron‐specific enolase (NSE).

### Duration

2.8

Information collection and scale rating for each patient will be finished within 180 min, and the whole enrollment work is expected to be finished in 12 months.

### Additional study parameters

2.9

The information on age, sex, nation, family history of psychiatric disorder, age of onset, time of BD diagnosis, education level, use of mood stabilizer in early stage, number of depressive and manic episodes, history of euthymia (yes/no), and premorbid adjustment ability will be collected.

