### Blinding and study group allocation

2.10

Subjects will be divided into AT or NT group according to whether they had a history of receiving systemic antidepressant treatment in early stage. The screening process will be finished by two senior psychiatrists, and then the following rating works will be handed over to other investigators, which could keep the latter investigators blind to the subjects’ group assignments.

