### Statistical analysis

2.19

The data obtained from questionnaires and basic information are expressed in “mean ± standard deviation” in the case of normal distributions and in median and quartile in the case of nonnormal distributions. The comparisons in scores of each scale between two groups will be made by Covariance Analysis; the Chi Square and Analysis of Variance (ANOVA) test will be used to test the consistency of match between groups for factors such as age, sex, MADRS scores, YMRS scores, PAS scores, use of mood stabilizers, age of onset, number of attacks, and so forth, and the factors with significantly different distributions between two groups will be used as covariates. Furthermore, the two groups of patients will be combined as a whole and then Multiple Linear Regression equations will be used to analyze the linear relationship between each factor and neurocognitive function. The test level is α = 0.05.

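### Education level is collected but not named as a covariate, and at best enters the cognitive comparisons only after a significant AT–NT difference, which loses precision and leaves part of any schooling bias in place

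*Protocol article*

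**What the plan says.** Additional study parameters lists the background data to be gathered, including "time of BD diagnosis, education level, use of mood stabilizer in early stage". Statistical analysis compares the groups by ANCOVA: "The comparisons in scores of each scale between two groups will be made by Covariance Analysis". The factors to be tested for balance are "factors such as age, sex, MADRS scores, YMRS scores, PAS scores, use of mood stabilizers, age of onset, number of attacks, and so forth". Education is not named, though the list is plainly illustrative. The rule for entering a covariate is that "the factors with significantly different distributions between two groups will be used as covariates", with "The test level is α = 0.05". A second, pooled regression is meant "to analyze the linear relationship between each factor and neurocognitive function", without a list of factors.

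The groups are not randomised. They are formed "according to whether they had a history of receiving systemic antidepressant treatment in early stage". The Discussion names PAS as the means of adjusting for premorbid function and the age limits as the guard against ageing effects. It does not mention education as a confounder or covariate.

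**The concern.** The objective main endpoints are tests of verbal fluency, verbal learning, digit span, digit symbol coding, trail making, Stroop and visual memory. Scores on such tests can be expected to vary with schooling. How strongly they do so in these patients is not in the document and is treated as an assumption below. No cognitive score from before exposure is listed, so education and PAS carry most of the information on premorbid level, and only PAS is named.

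Two things are at stake. First, a covariate that predicts the score sharpens the AT–NT contrast even when the groups are balanced, but under the stated rule a balanced factor is never used. Second, with groups formed by treatment history, schooling may differ between them. A difference too small to reach significance stays in the contrast and would be read as an effect of early antidepressants.

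**Working it through.** **Inputs from the document:** 62 per group; two-sided α = 0.05; δ = 0.3; covariates entered only if significantly different between groups.

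**Assumptions, not in the document:** correlation r between education and test score within groups of 0.3 to 0.5; scores and education on an SD scale; for the bias calculations, a true schooling difference of 0.3 SD.

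**The plan's own figure.** With δ = 0.3 and S = 1, a two-sided test at 80% power needs 175 per group, not 62. A value close to 62 (63) comes from a standardised difference of 0.5, or from δ = 0.3 with an unstated S of about 0.6. That is a separate matter. The present point uses 62 only as the planned size.

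**1. What escapes the balance test.** The largest non-significant observed difference is t(0.975; 122 df) × √(2/62) = 1.980 × 0.1796 = 0.356 SD. An observed imbalance of that size moves the unadjusted contrast by 0.356 × r, which is 0.11 SD (r = 0.3) to 0.18 SD (r = 0.5). A true schooling difference of 0.3 SD is missed by the balance test 62% of the time.

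**2. Precision from always adjusting.** Residual variance is multiplied by 1 − r², so the equivalent unadjusted size is 62/(1 − r²).

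| r | Standard error ratio √(1 − r²) | Equivalent n per group | Power at 0.3 SD (noncentral t) | Power at 0.5 SD (normal approximation) |
|---|---|---|---|---|
| no adjustment | 1 | 62 | 38.1% | 79.5% |
| 0.3 | 0.954 | 68.1 | 41.2% | 83.1% |
| 0.4 | 0.917 | 73.8 | 44.0% | 85.9% |
| 0.5 | 0.866 | 82.7 | 48.2% | 89.5% |

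**3. Bias and type I error with no antidepressant effect and a true schooling difference of 0.3 SD.** With education omitted, expected bias is 0.3 × r, or 0.09 to 0.15 SD. Simulation, 5,000 runs per setting:

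| Handling of education | Bias, r = 0.3 | Bias, r = 0.5 | Type I error, r = 0.3 | Type I error, r = 0.5 |
|---|---|---|---|---|
| Left out | 0.092 | 0.150 | 8.3% | 12.9% |
| Adjusted only if significant | 0.036 | 0.057 | 5.8% | 5.9% |
| Always adjusted | 0.001 | −0.001 | 5.2% | 4.8% |

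Direct calculation for the first row gives 7.9% and 13.2%, in agreement. Against δ = 0.3, the residual bias under the stated rule is 0.036/0.3 = 12% to 0.057/0.3 = 19%. With education left out it is 30% to 50%.

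**The case against.** The strongest reply is that the list of factors gives examples only, that education is an obvious member of the unlisted remainder, and that a complete covariate list is commonly left to the analysis plan, which is not shown. This stands to the extent that a reader might infer education is excluded, and the document does not say so. The 0.09–0.15 SD bias and the 8–13% error rate therefore describe the worst reading, not the plan as written. The reply does not remove the point, because the article does fix the rule of entry. Under that rule education gives no precision when balanced and is missed in most samples when the true difference is 0.3 SD.

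A second reply is that this is not separate from covariate selection. That is correct. Adding the word education to the list would not deliver the power gain. Only dropping the significance condition would.

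Third, an observed imbalance of 0.3 SD (p about 0.10) should not be paired with the 8–13% rate, which belongs to a population difference. For an observed imbalance fixed at 0.3 SD, unadjusted type I error is about 6.8%, 8.1% and 9.8% for r = 0.3, 0.4 and 0.5.

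Fourth, PAS and age may capture part of the education effect, so the figures are upper values if those are adjusted for. Nothing in the document shows that AT and NT differ in schooling.

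Last, eligibility starts at 18, and the Background cites a delay of 5–10 years from first episode to diagnosis. Schooling may thus have been shortened by the illness, and adjustment could remove part of what is being studied. This is a fair caution, and the fix allows for it.

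**Conclusion.** The point holds in a moderate form. Followed as written, the plan at best adjusts for education only after a significant group difference. Given r = 0.3–0.5, this forgoes a gain equivalent to about 6 to 21 patients per group (68 − 62 to 83 − 62). If schooling truly differs by 0.3 SD, it leaves a bias of about 0.04–0.06 SD. The accompanying rise in type I error, to about 6%, is small, so the case rests on lost precision and residual bias. The larger figures apply only if education is left out altogether, which the document does not establish. Both r and the schooling difference are assumptions. This is a worthwhile, cheap improvement and not a fatal flaw. It should be handled together with the general fault of selecting covariates by significance test.

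**What to change.** In Statistical analysis, prespecify education level, in the form in which it is collected, as a fixed covariate in the AT versus NT models of the objective cognitive tests and in the pooled regression, whatever the balance test shows. Report these estimates with and without education, since schooling may partly reflect early illness. Make the change in the same revision that replaces significance-based covariate selection; naming education while keeping that rule would not help.

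The cost is a line or two of text and no new variable. The article does not say whether education is recorded in years or in categories. It uses one degree of freedom per model if numeric and more if categorical. The with-and-without report adds one further model per test.

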
The current study attempts to clarify this question by making comparisons in neurocognitive function between bipolar patients who had a depressive episode as initial onset and being with and without systemic antidepressant treatment (received adequate dosage of antidepressants for 6 weeks at least) in early stage. Furthermore, the social functions and quality of life will also be investigated because both items are highly associated with cognitive functions and are indicative for functional rehabilitation. Apart from those, we will also study the influence of antidepressants used in early stage on impulsiveness, quality of sleep, and positive and negative affect. Lastly, peripheral neuron‐specific enolase (NSE) will be evaluated. NSE, a cell‐specific isoenzyme of glycolytic enolase, is known as a sensitive marker of neuronal damage (Isgrò et al., 2015). It has been showed that high level of serum NSE was related to mild cognitive dysfunction in patients with diabetic retinopathy (Yu et al., 2020) and that serum NSE levels of BD patients were significantly different from healthy controls (Akcan et al., 2018). In this regard, it is expected to examine the potential association between serum NSE level and cognitive function of BD patients. Finally, although it is mainly an explorative investigation and is informative for clinical practice regardless of outcomes, we expect that systemic antidepressant treatments in early stage could negatively affect the neurocognitive function, social functions, and quality of life of patients with BD.

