### Study design

2.1

This is a cross‐sectional study focusing on euthymic bipolar patients who had a depressive episode as initial onset. Participants were divided into two groups according to whether they had received systemic antidepressant treatment in the early stage: systemic antidepressant treatment (AT) group versus no systemic antidepressant treatment (NT) group.

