### Inclusion criteria

2.4

Patient's inclusion criteria are as follows: (1) diagnosisof BD according to the Diagnostic and Statistical Manual of Mental Disorders, Fourth Edition (DSM‐IV‐TR) with Structured Clinical Interview for DSM‐IV (SCID); current state of euthymia is defined by both scores of Montgomery–Åsberg Depression Scale (MADRS) and Young Manic Rating Scale (YMRS) < 7 (Cullen et al., 2016), lasting for 4 weeks at least before recruitment; (2) initiated with a depressive episode diagnosed with the MINI‐International Neuropsychiatric Interview (MINI); (3) age between 18 and 50 years; (4) participants comply with all procedures of study; and (5) participants must sign informed consent.

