### Scale assessments

2.12

COBRA will be used to assess subjective cognitive function, including verbal learning and memory, working memory, processing speed, executive functions, attention/concentration, and mental tracking. The summed scores of each item yield a total COBRA score, which is negatively correlated with subjective cognitive impairments.

SCWT, CVFT, and TMT‐B will be used to assess executive function, with higher scores indicating worse cognitive functioning.

DSFB, DSC of WAIS‐RC, and TMT‐A will be used to assess attention and processing speed. Higher scores for TMT‐A represent worse cognitive performance, and higher scores for DSFB and DSC of WAIS‐RS indicate better cognitive functioning.

VRP and VRC of WMS‐R will be used to assess visual memory, with higher scores indicating better cognitive functioning.

C‐AVLT will be used to measure verbal learning and memory domain. The higher number of word recall is associated with better verbal memory.

WHOQOL‐BRIEF will be used to assess the quality of life for the last 2 weeks prior to the assessment. It measures perceived quality of life for the domains of psychological health, physical health, social relationships, and environment as well as satisfaction with general health.

PSQI will be used to evaluate the quality of sleep for the last month, with a summed score ranging from 0 to 21, and a higher score indicates a worse sleeping quality.

PANAS will be used to detect the change in positive and negative affect. It is a self‐report instrument measuring the affective component of subjective well‐being, in which a higher score for each item refers to a higher degree for positive or negative affect.

MADRS will be used to assess the severity of depressive symptoms. The scale score ranges from 0 to 60, with a cutoff of 12 for depressive state.

YMRS will be used to assess the severity of manic symptoms. It includes 11 items, with a score not less than 6 indicating a manic state.

PAS will be used to evaluate the premorbid adjustment ability (Shi et al., 2013). PAS was designed for quantifying premorbid status in patients with schizophrenia originally, and now it has also been used in other field such as the study of mood disorders, coming to be regarded as a gold standard of retrospective assessment instrument.

MINI will be used to diagnose the initial episode of depressive disorder retrospectively.

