## DISCUSSION

3

Regarding the critical role of cognitive impairment in psychosocial disability and poorer quality of life, improving cognitive function has become a crucial goal in the management of BD patients. In this regard, increasing amount of research examining pharmacological and psychotherapeutic treatments was performed during the past decade (Alda et al., 2017; Solé et al., 2015). The research outcomes are inconsistent and no therapeutic intervention with sufficient efficacy is well‐established for improving cognitive dysfunction of BD yet (Miskowiak et al., 2016), although some of psychotherapeutic treatments or drugs appear as promising candidates. Many factors contributed to the discrepant outcomes such as poor randomization procedure, age of onset, number of depressive and manic episodes, severity of symptoms, and medications used specifically. In view of significantly delayed diagnosis of BD and common use of antidepressants in early stage, the effect of antidepressant agents on cognitive function has attracted increasing attention. But the data are still relatively rare, and the evidence is controversial. For example, a meta‐analysis estimated the relationship between antidepressant use and cognitive impairment and found that the odds of cognitive impairment were positively associated with antidepressant use in participants with an average age equal to or more than 65 years (odds ratio [OR] = 1.65), whereas those with participants aged less than 65 revealed an even stronger association (OR = 3.25) (Moraros et al., 2017); and also the study by Leng and colleagues illustrated that users of selective serotonin reuptake inhibitors and trazodone were as more as two to three times to develop dementia compared with the nonusers 5 years later, although the use of tricyclic antidepressants or other antidepressants was not involved in cognitive impairment (Leng et al., 2018). The evidence above suggests that antidepressant use could be a contributor for cognitive impairment of patients with mood disorder. Importantly, it is believed empirically that antidepressant treatment could deprave the natural course of BD and switch from depressive episode to episode of mania, hypomania, or mixed state (Viktorin et al., 2014), which may undermine the cognitive performance of bipolar patients (Goodwin et al., 2008). For instance, it was found that the higher number of manic and/or hypomanic episodes was negatively correlated with the cognitive performance of euthymic BD patients (*n* = 99) such as NCI, visual memory, and working memory in a 5‐year follow‐up longitudinal study (Sánchez‐Morla et al., 2019); furthermore, BD patients (*n* = 33), especially those with multiple mood episodes including mania, hypomania, and/or mixed state, showed severe impairments in emotional memory than healthy controls (*n* = 20) (Fijtman et al., 2020). Considering the significantly delayed diagnosis of BD and common use of antidepressants in clinical practice, such potential scathing effects should gather more attention. In contrast, another meta‐analysis suggested that antidepressants played a significant positive role in promoting psychomotor speed and delayed recall, with no significant difference between diverse types of antidepressants (Rosenblat et al., 2015). This is in line with the evidence from preclinical research that antidepressant agents could promote executive function and environmental information processing through integrating newborn neural cells into the hippocampal dentate gyrus (Tunc‐Ozcan et al., 2019). However, these data rarely came from clinical trial specifically focusing on the use of antidepressants in bipolar patients in early stage. To this end, the current study aims to clarify this issue by examining the cognitive function between bipolar patients who initiated with depressive episode and being with and without systemic antidepressant treatments in early stage. Additionally, the contemporary management of disease not only requires symptomatic relief but also pursues functional rehabilitation. Therefore, we will also examine the effect of antidepressant treatments in early stage on global function and quality of life of participants because both aspects are highly associated with cognitive function. Considering the potential influence of antidepressant use on progressing of course, the information on sleep quality and positive and negative affect will also be collected. Finally, the peripheral level of NSE will be tested to explore the potential biological mechanism of cognitive impairment.

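### No measure of how severe the early depression was is listed for collection or adjustment, so confounding by indication in the AT versus NT comparison is controlled only indirectly and in part

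*Protocol article*

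**What the plan says.** Section 2.1 forms the two groups "according to whether they had received systemic antidepressant treatment in the early stage". The Background sets the threshold for AT: "received adequate dosage of antidepressants for 6 weeks at least". Nobody is randomised, and both the abstract's objective and the hypothesis that closes the Background are causal: early antidepressants are expected to harm cognition.

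Section 2.9 lists the descriptive and clinical data. Among them are "use of mood stabilizer in early stage, number of depressive and manic episodes", together with age of onset, time of BD diagnosis, family history, education and premorbid adjustment. Section 2.19 tests balance on "factors such as age, sex, MADRS scores, YMRS scores, PAS scores, use of mood stabilizers, age of onset, number of attacks", ends that list open, and adjusts only for factors that differ significantly between the groups.

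On the first depression, section 2.12 says "MINI will be used to diagnose the initial episode of depressive disorder retrospectively". The limitations in 3.1 cover recall, the pooling of drug types and doses, and type II error.

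**The concern.** In a comparison by treatment received, the first rival explanation is the illness for which the treatment was given. It is plausible that patients with more severe early depression were more likely to complete an adequate course of at least six weeks, and that more severe early illness goes with worse cognition later. If both hold, AT would score worse than NT with no drug effect at all. That is the direction the authors expect, so the bias would look like confirmation.

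A variable that is never collected cannot be adjusted for in any later analysis. The gap therefore matters at the level of the data list, and a statistical analysis plan could not repair it.

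**Working it through.** **Step 1. Does any listed item measure early depressive severity?**

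| Item | Where | What it captures |
|---|---|---|
| MADRS | 2.4, 2.12, 2.19 | "MADRS will be used to assess the severity of depressive symptoms"; no retrospective use is described. In 2.4 the "current state of euthymia is defined by both scores of" MADRS and YMRS, each below 7, so it is a current and truncated score |
| MINI | 2.4, 2.12 | Diagnosis of the first episode; no severity score is described |
| HCL-32 | 2.11, 2.12 | Early hypomanic symptoms |
| PAS | 2.9, 2.12 | Adjustment before illness |
| Episode counts | 2.9, 2.19 | Number of episodes, no time window stated |
| Age of onset, time of BD diagnosis | 2.9 | Together, the length of the early stage |
| Early mood stabilizer use | 2.9 | Treatment, an indirect marker |
| Psychosis exclusion | 2.5 | Removes one severe subgroup from both arms |

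None measures how severe the early depression was. The last four rows give indirect, partial control. The episode counts are a weak substitute: without a window they may include episodes after the antidepressant, and the Background itself argues that antidepressants may provoke manic episodes, so the counts may lie on the causal path.

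**Step 2. How large could the bias be?** The documents give no figure for either input, so both are assumptions.

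- d = AT minus NT difference in early severity, in SD: 0.5 to 0.8 (assumed).
- r = correlation of severity with later cognition, read as SD of cognition per SD of severity: -0.2 to -0.3 (assumed).
- n = 62 per group, two-sided α = 0.05, planning δ = 0.3 (section 2.6).

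Spurious deficit B = d × |r|. The standard error of a standardised mean difference is √(2/62) = 0.180. With no drug effect, the chance of p < 0.05 on one test is Φ(B/0.180 - 1.96) + Φ(-B/0.180 - 1.96).

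| d | r | B (SD) | B / 0.3 | Chance of p < 0.05 |
|---|---|---|---|---|
| 0.5 | -0.2 | 0.10 | 33% | 8.6% |
| 0.5 | -0.3 | 0.15 | 50% | 13.3% |
| 0.8 | -0.2 | 0.16 | 53% | 14.5% |
| 0.8 | -0.3 | 0.24 | 80% | 26.7% |

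A wider assumed range runs from 0.3 × 0.2 = 0.06 SD (20% of 0.3; chance 6.3%) to 0.8 × 0.4 = 0.32 SD (107%; chance 42.9%). None of these figures gives credit for the partial control in Step 1.

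**Step 3. Is δ = 0.3 a standardised effect?** Section 2.6 gives no SD. With SD = 1, two-sided 5% and 80% power, n = 2 × (1.960 + 0.842)² / 0.3² = 174.4, so 175 per group, which does not reproduce 62. The stated 62 corresponds to a standardised effect of 2.802 × √(2/62) = 0.50. Against 0.50, a B of 0.10 to 0.24 is 20% to 48%. The sample-size mismatch is a separate matter; here it only affects the yardstick.

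**Step 4. Would the significance rule in 2.19 be enough if severity were recorded?** With 62 per group, the chance that an imbalance reaches p < 0.05 is about 39% for 0.3 SD, 80% for 0.5 SD and 99% for 0.8 SD. A difference of 0.5 SD would thus be left unadjusted about one time in five, and one of 0.3 SD about three times in five.

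**The case against.** The case on the other side has several sound parts.

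- A reader might infer that the question cannot be answered at all. The documents do not support that. The psychosis exclusion, the shared diagnostic threshold for the first episode, the dates of onset and diagnosis, early mood stabilizer use and the pooled regression all give some control, and the article calls itself mainly exploratory. Inference is weakened, as in other observational drug comparisons.
- A reader might take the Discussion's list, "age of onset, number of depressive and manic episodes, severity of symptoms, and medications used specifically", as the authors conceding the point. It is not that. The list explains inconsistent results among studies of treatments meant to improve cognition, and says nothing on who receives antidepressants early.
- A reader might call the episode count a lifetime total. Sections 2.9 and 2.19 state no window, so that is an inference.
- Severity as the route into AT is plausible but not documented. The route the Background gives is misdiagnosis or delayed diagnosis, and the length of the delay can be derived from recorded items.
- The article is condensed. Section 2.11 gives a shorter parameter list than 2.9, the list in 2.19 is open-ended, and item-level MINI data may exist. That leaves room for doubt, but 2.9 is a specific list, and nowhere is severity named as recorded or as a candidate covariate.
- The magnitudes rest wholly on assumption. That stands, and they are offered only to show possible size.

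What remains is that no listed item measures early severity and that 3.1 does not name confounding by indication.

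**Conclusion.** The point holds as a gap in measurement and adjustment. Confounding by indication is controlled only through proxies, and the residual bias could run in the hypothesised direction. Under the assumed inputs it is 0.10 to 0.24 SD, that is, one third to four fifths of a standardised δ of 0.3. Only the most extreme input pair considered (0.8 SD and a slope of 0.4) reaches the whole of it. With no drug effect, the chance of a nominally significant result on one test rises from 5% to between 9% and 27% over the main range. These figures depend on the assumed severity difference and slope and on a single comparison without credit for the proxies; they are not estimates for this population. The change should be made because a variable never collected cannot be adjusted for later, and because the interview and record check that could supply it are already planned.

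**What to change.** In 2.9 and 2.11, during the retrospective MINI and the check of medical records, record early-stage depressive severity using only information that precedes the first systemic antidepressant course. For NT, define a comparable early-stage window in advance. The fields are:

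- MINI depressive symptom count for the initial episode;
- hospitalisation or suicide attempt (yes/no);
- number of depressive episodes, and time ill, before that point.

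Do not use the full duration of a treated episode. If treatment began within it, part of that duration is post-exposure, and adjusting for it could remove part of any real effect. Counting episodes and time ill up to the first course also covers the case where the antidepressant was started for a later episode.

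In 2.19, include this measure as a pre-specified covariate in every AT versus NT comparison, whether or not it differs significantly. In 3.1, state residual confounding by indication as a limitation, and word the results as association.

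The cost is a few extra fields in work already planned and one or two more covariates. The measure is retrospective and imperfect, and shares the recall problem that 3.1 already accepts for the treatment history, so adjustment will reduce the confounding but not remove it.
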